#### Blinding (Masking)

Considering the nature of the intervention proposed, this study is designed as an open-label study; the participants and the intervention implementing team will not be blinded to the intervention. However, the statistician performing data analyses will be blinded to group assignments.

#### Baseline Assessment

Demographic details, such as age, gender, occupation, education, BMI, disease conditions details, and list of drugs used (including FRIDs with their costs and orthostatic hypotension details) will be collected from all the participants. Drug details, such as the name of the drug, indication, frequency, route of administration, and duration of use will also be collected. The rationality of the prescriptions will be assessed by the World health Organization prescription indicators.

Participants will then be asked about their previous fall history using the fall history questionnaire of McCrum 2020 [8] and their concern for falls assessed by the Fall Efficacy Scale [9,10]. Quality of life will be assessed by administering the EQ-5D-5 L questionnaire. Once the baseline data collection is completed, they will be assessed for fall risk. The fall risk assessment will be conducted by a staff nurse using the Timed Up and Go test and the Tinetti Performance-Oriented Mobility Assessment Tool.

### Intervention Details

Clinical pharmacologists will do steps 1 and 2 of the ARMOR tool for the recruited participants’ prescriptions and prepare a summary report of all the recruited participants’ prescriptions.

### Test Group

Participants randomized to this group will be managed using the ARMOR tool–based deprescribing intervention, which contains 5 steps—Assess, Review, Minimize, Optimize, and Reassess. A clinical pharmacologist provides a summary report of steps 1 and 2 of the ARMOR tool to the treating physician. The treating physician will complete steps 3 to 5.

### The ARMOR tool

The ARMOR tool [11] is designed to guide health care professionals in a structured approach to medication management, emphasizing the importance of regular assessment, review, modification, optimization, and reassessment. It promotes patient-centered care and aims to enhance medication safety and effectiveness.

#### Step 1: Assessment

A comprehensive assessment of the patient's medication regimen will be done during this step.

#### Step 2: Review

In this step, the pharmacologist along with the treating physician will review the assessment findings (ie, the overall effectiveness and necessity of each medication) and will identify any potential risks or harms associated with continued use.

#### Step 3: Modify

Based on the review submitted, the clinician may consider a deprescribing intervention for medications that are no longer necessary, ineffective, or potentially harmful. If required clinicians will consider adjusting dosages, changing formulations, or switching to alternative medications.

#### Step 4: Optimize

In this step, clinicians will focus on enhancing the patient's medication regimen to achieve the best possible outcomes. They may initiate new medications when necessary, optimizing dosages for maximum efficacy, and addressing any identified gaps in therapy.

#### Step 5: Reassess

After modifications and optimization, the clinician will continue to monitor the patient's response to the medication changes. They reassess the patient's symptoms, side effects, and overall treatment outcomes.

### Control Group

Participants randomized to the usual care group will receive treatment as per the standard practice or protocol. As there are no established gold standards for effective, deprescribing interventions, usual care is chosen as a comparator.

### The Follow-Up Phase

Each participant will be followed for a period of 1 year after their enrollment into the study. Both groups will be followed up for 1 year. Each participant will be given a diary to record the falls and other adverse events. They will be followed up monthly over the phone for falls and for occurrence of other adverse events and for improving adherence to the intervention protocols of the study. Every 3 months, they will be followed up physically to assess fall risk, inquire about any fall history, and note any adverse events during that period.

### Unscheduled Visits

In case of any adverse events and serious adverse events during the study period, there may be an unscheduled visit planned for the concerned participant. The details of any such event will be recorded and appropriate treatment will be provided. When trial participants experience an injury, adverse event, or serious adverse events, they will be noted, and appropriate treatment will be given.

### End of Study

At the end of the study (after 1 year of follow-up), the complete information, such as the number of drugs with their details, fall history, fall concern, fall risk, and quality-adjusted life-year will be assessed. The rationality of the prescriptions will be assessed by the World Health Organization prescription indicators. Figure 1 provides an overview of the study methodology.

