#### Incremental Cost-Effectiveness Ratio (ICER)

Incremental Cost-Effectiveness Ratio (ICER) will be calculated by dividing the difference in costs between the interventions by the difference in outcomes. The ICER represents the additional cost per unit of outcome achieved by one intervention compared to another.

We will be following the intention-to-treat strategy to analyze the data. Therefore, even participants who discontinue but have at least 1 follow-up will be included in the study to achieve the required sample size, taking into account their age and health status.

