### Ethical Considerations

The study will be conducted as per the ICMR National Bioethical Guidelines 2017 [13] and New Drugs and Clinical Trial Rules 2019 [14]. The study received approval from All India Institute of Medical Sciences Bibinagar, Institutional Ethics Committee (AIIMS/BBN/IEC/JUNE/2023/294) on June 16, 2023.

Eligible participants who are willing to participate in the study will be enrolled after obtaining written informed consent.

Confidentiality of participation will be maintained, and personal identity will not be revealed during data collection, analysis, presentations, and publications. Study records will be preserved for 3 years and will be made available only to authorized persons conducting the study and to the funding agencies without revealing participant identities.

Reimbursement of Rs 500 (about US $6) per visit will be provided for participation in the study, as participants will be asked to visit the hospital every 3 months after their enrollment into the study.

For any foreseeable and unforeseeable complication, adequate compensation will be provided depending on the nature of the injury or illness. In addition, trial insurance coverage will be provided for any unforeseeable risks related to the study.

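### As written, utility is placed only at baseline and the QALY only at 12 months, so any QALY gain from preventing temporary fall-related losses would be attenuated and noisier

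*Protocol article*

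**What the plan says.** All references are to the protocol article.

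- **Baseline Assessment:** "Quality of life will be assessed by administering the EQ-5D-5 L questionnaire". This is the only mention of EQ-5D-5L, and no other utility instrument is named.
- **End of Study:** the timing is "At the end of the study (after 1 year of follow-up", and the items listed include "fall history, fall concern, fall risk, and quality-adjusted life-year will be assessed". This is the only mention of the QALY. No instrument is named here.
- **The Follow-Up Phase, calls:** "They will be followed up monthly over the phone for falls and for occurrence of other adverse events", with adherence as a further purpose.
- **The Follow-Up Phase, visits:** "Every 3 months, they will be followed up physically to assess fall risk, inquire about any fall history, and note any adverse events". The Abstract likewise describes the 3-monthly assessments as fall-risk assessments.
- **Ethical Considerations:** "participants will be asked to visit the hospital every 3 months after their enrollment into the study", with reimbursement for each visit.
- **Incremental Cost-Effectiveness Ratio (ICER):** the ratio is "calculated by dividing the difference in costs between the interventions by the difference in outcomes". The unit of outcome is not named.

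Cost-effectiveness is part of the stated objective. The article does not say how utilities become QALYs.

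**The concern.** A QALY is an area under a utility curve over time. With utility known only at months 0 and 12, the path between has to be assumed, and the usual assumption is a straight line. A fall does not follow a straight line: utility drops suddenly and may recover within weeks or months. The sample-size section assumes a fall incidence of 73%, so such events could be common in this trial, although the article does not say how many of them would lower utility or for how long.

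At stake is the part of the QALY difference between arms that comes from preventing temporary losses. Utility not collected at months 3, 6 and 9 cannot be recovered by any later analysis plan, so the matter belongs in the visit schedule.

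**Working it through.** The article gives no QALY, utility or ICER figure, so there is nothing to reproduce. The check is an illustration.

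**Inputs from the article:** EQ-5D-5L at month 0; QALY at month 12; visits at months 3, 6 and 9 with no utility measure listed.

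**Assumptions, not in the article:** EQ-5D-5L is repeated at month 12; linear interpolation; one step-shaped loss of size d per participant, absent at baseline, that either heals fully or persists. The table uses d = 0.10. Results scale in proportion over a range of 0.1 to 0.3, so at 0.3 every entry is three times as large.

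**Formulas (QALYs lost):**
- True loss = d × (months with the loss before month 12) / 12.
- Two points = d × 6/12 if the loss is present at month 12, otherwise 0.
- Five points = d × (sum of weights at the visits where the loss is present) / 12, with weights 1.5, 3, 3, 3 and 1.5 months at months 0, 3, 6, 9 and 12.

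| Loss of 0.10 | True | Two points | Five points |
|---|---|---|---|
| Months 4 to 7, heals | 0.10 × 3/12 = 0.025 | 0 | 0.10 × 3/12 = 0.025 |
| Months 2 to 8, heals | 0.10 × 6/12 = 0.050 | 0 | 0.10 × 6/12 = 0.050 |
| Months 3.5 to 5.5, heals | 0.10 × 2/12 = 0.0167 | 0 | 0 |
| From month 1, persists | 0.10 × 11/12 = 0.0917 | 0.050 | 0.10 × 10.5/12 = 0.0875 |
| From month 6, persists | 0.10 × 6/12 = 0.050 | 0.050 | 0.10 × 7.5/12 = 0.0625 |
| From month 10, persists | 0.10 × 2/12 = 0.0167 | 0.050 | 0.10 × 1.5/12 = 0.0125 |

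The two-point error therefore goes both ways. Healed losses vanish, late persistent ones are inflated (three times at month 10), and early persistent ones are understated.

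**Average over onset.** Single cases do not show the net effect on a group mean. Take onset uniform over 12 months and count in decrement-months, so that d cancels.

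*3-month loss.* It is present at month 12 only if onset is after month 9, probability 3/12 = 25%, so 75% of such losses score zero.
- Two-point mean: 0.25 × 6 = 1.5.
- True mean: 0.75 × 3 + 0.25 × 1.5 = 2.625.
- Captured: 1.5/2.625 = 57%.

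*6-month loss.* It is present at month 12 with probability 50%, so 50% score zero.
- Two-point mean: 0.5 × 6 = 3.0.
- True mean: 0.5 × 6 + 0.5 × 3 = 4.5.
- Captured: 3.0/4.5 = 67%.

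*Five points.* By quarter of onset, a 3-month loss scores 3, 3, 3 and 1.5, mean 2.625. A 6-month loss scores 6, 6, 4.5 and 1.5, mean 4.5. Both equal the true mean.

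*Error for one participant (root mean squared, decrement-months).* Going from two to five points reduces it from 3.5 to 0.4 for 3-month losses and from 4.9 to 0.6 for 6-month losses.

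*Shorter losses.* For a 1-month loss, two points capture 0.5 of 0.958 (52%) and five points 0.875 of 0.958 (91%). The root mean squared error falls only from 1.85 to 1.32.

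**Between-arm difference.** If the arms differ only in how many such losses occur, the difference in mean QALYs shrinks by the same factors. If QALYs were the ICER denominator, the whole QALY difference came this way and costs were unchanged, the ratio would be multiplied by 2.625/1.5 = 1.75 for 3-month losses or 4.5/3.0 = 1.5 for 6-month losses.

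**The case against.** **The schedule may be fuller than the article shows.** No sentence says that utility is measured twice only. The flowchart is not shown, the end-of-study items are given as examples, and the visit list also omits drug and cost recording, which the ICER would need. A reader might infer that the protocol fixes EQ-5D-5L at exactly two time points. The text does not go that far, and even the month-12 administration is an inference from the QALY being named there. What remains is that The Follow-Up Phase itemises the interim contacts and utility is not among them, and the Abstract agrees. If the full schedule has it, this section needs correcting.

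**The ICER may not use QALYs.** This stands. A reader might infer that the ICER denominator is wrong, but the article leaves the outcome unit open. It could be falls avoided, which the diaries, calls and visits record.

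**Two points are not blind to falls.** This stands for a comparison of means. A reader could conclude from the healed-loss rows that fall-related losses are almost entirely missed. On average more than half is captured, because overstated late losses partly offset the missed ones. The result is attenuation and noise.

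**Quality of life need not act through falls.** This stands in part. The Introduction links polypharmacy itself to poorer quality of life, so a sustained gain from a lighter drug burden is possible, and it would be visible at month 12. Under linear interpolation it would still be mis-sized unless it began near month 6: one starting at month 1 would be credited 0.050 of 0.0917.

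**Losses that span exactly one visit flatter the fix.** This is fair for single cases. A loss wholly between visits scores zero with five points too, and a 1-month loss that spans an interim visit is credited with three months. The averages over onset do not depend on such a choice.

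**The QALY method is analysis-plan detail.** True of the area calculation and baseline adjustment, but not of which visits collect the questionnaire.

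**Conclusion.** The point holds as a conditional one and calls for a cheap improvement. It is not a contradiction or a wrong figure in the protocol. On the schedule as written, utility is available at the two ends of the year at most.

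With linear interpolation and a step loss whose onset is uniform over the year, about 43% of the QALY loss from 3-month episodes and 33% from 6-month episodes goes unrecorded on average (100% minus 57% and 67%). These shares do not depend on the decrement, but they do depend on duration and on the uniform-onset assumption, and the article informs neither. The absolute size cannot be stated from the document.

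The consequence is confined to QALY gains that arise through prevented temporary losses, and it reaches the ICER only if QALYs are chosen as its outcome.

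**What to change.** - **The Follow-Up Phase:** add EQ-5D-5L to the existing 3-, 6- and 9-month visits in both arms. If the full schedule already contains it, align this section with that schedule.
- **End of Study:** name EQ-5D-5L at month 12, and state that QALYs are the area under the five-point utility curve, adjusted for baseline utility.

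The cost is one short questionnaire at three visits that participants already attend: a few minutes each and some extra data entry. Brief losses that fall wholly between visits will still be missed.

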**Figure 1 figure1:**
[figure not shown]
Flowchart of the overall study methodology. ARMOR: Assess, Review, Minimize, Optimize, and Reassess; FRID: fall risk–increasing drug; TUG: Timed Up and Go; POMA: Tinetti Performance-Oriented Mobility Assessment.

### Adverse Events or SAE

Adverse events will be recorded in the adverse event form. The details will be collected in the adverse drug reaction reporting form and causality assessment will be done to find the adverse event’s association with FRIDs. In the case of SAE, we will be recording and reporting the serious adverse events to regulatory authorities.

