**Results:**

The study received a grant from the Indian Council of Medical Research–Safe and Rational Use of Medicine in October 2023. The study is scheduled to commence in April 2024 and conclude by 2026. Efficacy will be measured by fall frequency and changes in fall risk scores. Cost-effectiveness analysis will also include the incremental cost-effectiveness ratio calculation. Adverse events related to deprescription will be recorded.

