#### Data and Safety Monitoring Board

A Data and Safety Monitoring Board will be constituted for this study independent of the study team members. The team will look into the safety of the intervention proposed with an interim analysis report.

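### Adverse event causality is defined against FRIDs, not against withdrawing or changing drugs, so the stated procedure does not identify the deprescribing-related events the abstract says will be recorded

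*Protocol article*

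**What the plan says.** Two statements in the protocol article bear directly on attribution.

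- **Adverse Events or SAE** sends event details to a drug-reaction form, "The details will be collected in the adverse drug reaction reporting form", and then fixes the causal question: "causality assessment will be done to find the adverse event’s association with FRIDs". No other section describes a causality assessment.
- **Abstract, Results** commits to a category defined by the intervention: "Adverse events related to deprescription will be recorded".

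The intervention is set out in the ARMOR steps. Under Step 3, "the clinician may consider a deprescribing intervention for medications that are no longer necessary, ineffective, or potentially harmful"; the same step also allows changes of dose or formulation and substitution of another drug, and Step 4 allows new drugs to be started.

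Other sections describe how safety information is gathered and reviewed.

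- **The Follow-Up Phase**: "Each participant will be given a diary to record the falls and other adverse events", and "Both groups will be followed up for 1 year", with monthly calls and three-monthly visits that also ask about adverse events.
- **Step 5: Reassess**, on clinicians using the tool: "They reassess the patient's symptoms, side effects, and overall treatment outcomes".
- **Data and Safety Monitoring Board**: "The team will look into the safety of the intervention proposed with an interim analysis report".

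**The concern.** A causality rating is informative about an intervention when it asks whether that intervention caused the event. Here the experimental exposure is a change in drug treatment, usually a removal, whereas the rating asks about the drugs the intervention aims to reduce. An event that arises because a drug was taken away is not, on an ordinary reading, an adverse reaction to that drug.

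The main harms one would look for in a deprescribing trial are withdrawal reactions and return of the condition the drug was treating. The abstract says events of this kind will be recorded, and the DSMB is asked to consider the safety of the intervention. If the form captures relation to FRIDs alone, these events will sit among the unrelated ones. A later analysis plan can only summarise the relatedness that was collected; it cannot reliably create a rating afterwards.

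**Working it through.** No arithmetic applies. The point depends on which exposure the causality rule names, not on a rate, power or sample size. The check has three steps.

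**1. Compare the exposure tested with the exposure rated.**

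- Tested: drugs stopped, altered in dose or formulation, or replaced (Step 3), and drugs started (Step 4).
- Rated for causality: FRIDs (Adverse Events or SAE).
- Promised as a recorded category: events related to deprescription (Abstract, Results).

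The first and third match each other. The second does not match either.

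**2. Pass typical events through the stated rule.**

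- *Reaction to a FRID that is still being taken.* The rule covers it. It can occur in either arm.
- *Reaction to stopping or reducing a FRID.* The abstract's category needs it. The rule does not name it, and an assessor could class it as related or unrelated depending on how widely association is read.
- *Return of the treated condition after a drug is stopped.* The abstract's category needs it. The cause is the absence of the drug, so a rating of association with the drug has no natural place for it.
- *Reaction to a substituted or newly started drug that is not a FRID.* This is a consequence of the tool's Step 3 or Step 4, and the rule does not cover it.
- *Event with no link to any drug or drug change.* Rated unrelated, correctly.

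Of the five types, the first and last are classified clearly. The middle three, which are the ones that can follow from a drug change, are left ambiguous or outside the rule.

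**3. Check what is captured without attribution.**

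The diary, the monthly calls and the three-monthly visits carry no causality condition and apply to both groups for one year. Unscheduled visits may be arranged for events. Serious adverse events are recorded and reported with no relatedness condition. All five event types should therefore enter the data in both arms, and total events can be compared by arm. What the stated procedure does not provide is the label that separates the middle three types from the rest.

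**The case against.** The strongest case on the other side has four parts.

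*Harm is assessed.* A reader might infer from the causality sentence that harms of deprescribing are never assessed. The article does not support that. All-cause collection on one schedule in two randomised groups allows a between-arm comparison, which reflects withdrawal harm without any individual judgement. Step 5 of the tool and the DSMB add further review. This part stands, and it limits the point to attribution.

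*The rule is not exclusive.* The sentence names FRIDs but does not say that other causes will be ignored, and the abstract's statement could be read as complementary. It is therefore too strong to say that no event could ever be classed as related to deprescribing, or that the promised category would be empty. It remains true that the article states a rule for one exposure and none for the exposure it promises to report on.

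*The forms are not shown.* The adverse event form or the drug-reaction form may already have a field for drugs stopped and dates of change, and form content is commonly left to the full protocol. That possibility is real. It does not remove the mismatch, because the causal target is stated in the article and differs from the abstract's.

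*No biased safety report is documented.* A reader might infer that the DSMB will see a relatedness table tilted towards deprescribing. No section describes such a table or restricts the DSMB to related events. Deprescribing is optional in the test arm, and usual care does not forbid stopping drugs, so the split of event types between arms is not fixed by design either. This part stands too.

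**Conclusion.** The point holds in a limited form. The article defines causality against FRIDs, the exposure the intervention aims to reduce. It does not define it against the withdrawal or change of drugs that is being tested. The stated procedure therefore does not identify the deprescribing-related events that the abstract says will be recorded, and the two sections need to be reconciled.

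What is lost is attribution of events such as withdrawal reactions or return of the treated condition. The all-cause comparison between arms remains available, and the sample size and the analysis of falls are not affected. The magnitude cannot be estimated: the article gives neither a rate of withdrawal events nor a proportion of participants whose drugs will be changed.

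The conclusion rests on two assumptions: that association with FRIDs is read in its ordinary sense, as an effect of taking them, and that the forms not shown follow the rule as printed. If the forms already capture relation to a drug change, a short clarification of the text would be enough. Otherwise the matter should be corrected, preferably before data collection.

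**What to change.** Reconcile the Adverse Events or SAE section with the abstract as follows.

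1. Keep the rating of association with FRIDs. Add, for every adverse event in both arms, a second rating: relation to any drug stopped, reduced, switched or started since enrolment, with the drug and the date of the change. Using it in both arms matters because drugs can also be changed under usual care.
2. State that events rated as related on this second question to a drug stopped or reduced, or switched as part of deprescribing, make up the category named in the abstract. Report relation to newly started drugs within the same rating but separately.
3. Report to the DSMB, by arm, all adverse events and all serious adverse events regardless of causality, with both ratings alongside.
4. Make the all-cause comparison by arm the main safety comparison. The trial is open-label and the article describes no masked causality assessors, so both ratings may be influenced by knowledge of the arm and should be supportive.

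The cost is one added rating with a date, one additional table and slightly more data entry. No treatment rule or sample size changes. The rating is cheap to collect from the start and hard to reconstruct later.
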